# Can we decrease the duration of basal thumb joint distraction for early osteoarthritis from 8 to 6 weeks? Study protocol for a non-inferiority randomized controlled trial

**DOI:** 10.1186/s13063-021-05283-9

**Published:** 2021-05-01

**Keywords:** Osteoarthritis, Thumb, Carpometacarpal Joint, External fixator, Complications, Treatment

## Abstract

**Background:**

To our knowledge, to date, 52 patients with thumb carpometacarpal osteoarthritis (CMC1 OA) were treated with joint distraction. So far, most patients experienced improved physical function and less pain. After 2 years, only 1 patient proceeded to trapeziectomy. This study assesses if we can safely lower the distraction duration from 8 to 6 weeks for CMC1 joint distraction, maintaining the improvement in physical function and pain.

**Methods:**

This is a monocenter randomized controlled non-inferiority trial that includes patients younger than 65 years of age with ongoing symptoms of CMC1 OA and an established indication for surgery. All patients will be treated with CMC1 joint distraction. The primary outcome is to assess whether 6 weeks of joint distraction is not inferior to 8 weeks in terms of physical function at 1 year after surgery. Secondary outcomes will identify differences between groups at 1 year in pain intensity, patient satisfaction, hand health status, adverse event rates, treatment failure, differences in thumb strength and range of motion, and radiographic changes.

**Discussion:**

If safe, the duration of basal thumb joint distraction can be reduced to 6 weeks, reducing patient burden. Because this is a relatively new treatment, this trial will provide greater knowledge of potential adverse events. This knowledge allows for more informed decision making for patients considering CMC1 distraction treatment. Future studies can directly compare joint distraction to other treatments of CMC1 joint arthritis like splinting and trapeziectomy.

**Trial registration:**

Central Committee on Research Involving Human Subjects (CCMO), NL68225.100.18; registered on 9 August 2019. Medical Research Ethics Committees United (MEC-U), R19.003; registered on 9 August 2019. Netherlands Trial Register, NL8016; registered on 15 September 2019.

**Supplementary Information:**

The online version contains supplementary material available at 10.1186/s13063-021-05283-9.

## Background

One out of three people aged 55 years and older has radiographic signs of carpometacarpal osteoarthritis of the thumb joint (CMC1 OA) [1–3]. The prevalence increases with ageing to 90% for adults aged 80 years and older [1–3]. Patients with symptoms of CMC1 OA are initially offered non-operative treatment including splints, analgesics, and hand therapy to reduce pain [4]. If these interventions do not offer sufficient relief, surgical treatment can be considered [4–6]. There are numerous variations in surgical treatment for CMC1 OA. There is, however, no evidence for the superiority of individual techniques regarding pain and functional outcome [5–7]. Trapeziectomy alone, or combined with ligament reconstruction and tendon interposition or suspension arthroplasty, carries the long-term risk of metacarpal subsidence with or without persisting symptoms [5–9]. Prostheses are associated with loosening, subluxation, fracture, and synovitis, potentially requiring revision surgery [5–10]. Arthrodesis of the CMC1 joint reduces range of motion and has the associated risk of non-union resulting in revision surgery [11]. For patients with persisting symptoms of CMC1 OA requiring surgical intervention at a relatively young age, other techniques that preserve the joint and are less invasive may be more desirable.

Joint distraction is a joint sparing treatment for relatively young patients (< 65 years of age) with symptoms of OA and aims to postpone or prevent an invasive surgical intervention [12–15]. Previous evidence on ankle and knee OA shows that joint distraction can result in sustained clinical improvement with actual repair of joint cartilage after treatment [12, 14–18]. Van der Woude et al. [15] showed persisting pain reduction and greater physical function compared to baseline at 5 year follow-up among patients who underwent knee distraction. Another study demonstrated an almost 50% (8/17) joint survival rate after 9 years [14].

Joint distraction is also feasible for the osteoarthritic CMC1 joint [19]. Nowadays, to our knowledge, more than 50 patients with persisting symptoms of CMC1 OA despite non-operative therapy were treated with CMC1 joint distraction. Recent follow-up results of 20 patients who underwent CMC1 joint distraction shows that in 19 of 20 patients an invasive surgical intervention was postponed for at least 2 years (unpublished data). On average, all patients experienced less pain and better physical function after 2 years. Unpublished data of the first 5 patients shows that all patients were still satisfied 5 years post-distraction without further surgical interventions.

Distraction of the CMC1 joint is currently applied for 8 weeks. However, the duration of knee joint distraction has been decreased from 8 to 6 weeks [17]. This is based on results of 2 previous studies that report similar clinical results at 1 year and less pin tract infections among patients in the 6-week group [17, 18]. Pin tract infections occurred in 85% of patients in the 8-week group versus 55% in the 6-week group [17]. During CMC1 joint distraction, pin-tract infections occur in approximately 1 of 3 patients and are usually adequately treated with oral antibiotics (unpublished data of 40 patients). It is unknown if shortening of the CMC1 joint distraction duration from 8 to 6 weeks will also result in less adverse events and still achieve sufficient clinical benefits for patients. Therefore, we designed this study protocol for a randomized controlled non-inferiority trial to compare 6 weeks with 8 weeks of CMC1 joint distraction.

### Study objectives

The primary objective is to assess if 6 weeks of CMC1 joint distraction is not inferior to a duration of 8 weeks. Our primary outcome is physical function measured with the Patient-Reported Outcomes Measurement Information System Physical Function for the Upper Extremity (PROMIS UE) at 1 year after distraction.

Our secondary objectives are:
We hypothesize that there is no difference between groups in terms of pain intensity, patient satisfaction, joint stiffness, thumb function, range of motion, and strength at 1 year.We hypothesize that there is no difference in hand health status measured with the Michigan Hand Outcome Questionnaire (MHQ) between the 6-week and 8-week group at 1 year.We will investigate if there is a difference in adverse event rate and treatment failure at 1 year.We will measure minimal joint space width on radiographs at 1 year and test if there is a difference between the two groups.We will assess symptoms of depression and catastrophic thinking (captured by 2 short questionnaires) since there is mounting evidence that psychosocial factors influence symptom intensity and magnitude of physical limitations among patients with CMC1 OA [20–22]. We will test if these, and other factors, are independently associated with physical function and hand health status.To study the long-term effects of joint distraction in the treatment of CMC1 OA, we will test all hypotheses mentioned above at 2 years and 5 years post-distraction.

## Methods/design

### Study design

This is a monocenter randomized controlled non-inferiority trial conducted at the St. Antonius Hospital in the Netherlands: a peripheral teaching hospital in a large urban area. Patients will be randomly assigned to group A or B using a secured computer programme (Research Electronic Data Capture (REDCap)). All patients are treated with continuous CMC1 joint distraction by placing an external distractor device over the affected joint. The distractor device will be removed after 6 weeks among patients in group A; for patients randomized to group B, the device is removed after 8 weeks.

#### Participants

The study population consists of 68 patients with ongoing symptoms of CMC1 OA despite non-operative treatment. All patients have an established indication for an invasive surgical intervention (such as a trapeziectomy) at a relatively young age (< 65 years).

#### Inclusion criteria

In order to be eligible to participate in this study, patients must meet all of the following criteria:
Age < 65 yearsEaton-Glickel classification II or III on radiographs [23]Failed non-operative treatment (e.g. splint for at least 3 months)Established indication for invasive surgical treatment for CMC1 OA according to standard clinical practiceWillingness to participate in the study and able to understand distractor maintenance and hygiene instructions

#### Exclusion criteria

Patients who meet any of the following criteria will be excluded from participation in this study:
Severe CMC1 OA with Eaton-Glickel grade IV on radiographs [23]Joint subluxation of > 30%Surgical treatment of the CMC1 joint in the pastInflammatory or rheumatoid arthritis present or in past medical historyUse of immunosuppressive or chemotherapeutic drugsPrevious corticosteroid injection in the CMC1 jointHypermobility syndrome or syndromic diseasesUnable or unwilling to attend follow-up appointments

### Surgical procedure

CMC1 joint distraction will be performed by one of two hand surgeons with experience in this procedure. Both surgeons are hand fellowship trained and certified by the Federation of the European Societies for Surgery of the Hand. They have developed and performed all CMC1 joint distractions (*n* = > 60) since the start of this treatment in 2014. Their level of experience is a category 5— according to the classification by Jin Bo Tang—based on the pioneering contribution both surgeons made in developing this technique [24]. Patients will be operated under regional anaesthesia, unless patients prefer general anaesthesia. All patients receive systematic antibiotics perioperative (2 g cefazoline intravenous). An external distractor device (Osteo-x, Osteotec, Dorset, UK) is placed over the affected CMC1 joint (Fig. 1a). The device is anchored transcutaneous with 2 proximal k-wires in the trapezium bone and 2 distal k-wires in the first metacarpal bone (Fig. 1b). Subsequently, the distractor device is distracted 3 mm intraoperative. The k-wires are cut 1.0 to 1.5 cm above the device (Fig. 1c). Adequate positioning of the distractor and proper placement of the k-wires in the trapezium and metacarpal bone is checked with video-fluoroscopy during the procedure. The position of the device is checked with standard radiographs at set postoperative intervals (Figs. 2 and 3). Patients are given a custom-made thermoplastic splint to cover and protect the distractor device. Hygiene instructions regarding pin entry point maintenance will be given. Patients are discharged after surgery (daycare), unless the unlikely event occurs that a hospital admission is needed. During the period of distraction, patients will be seen at the outpatient clinic at set post-operative intervals.

**Fig. 1 Fig1:**
[figure not shown]
**a** The distractor device. **b** Drawing of the trapezium bone and metacarpal bone. **c** Distractor device in situ with 2 k-wires in the trapezium and 2 in the metacarpal bone

**Fig. 2 Fig2:**
[figure not shown]
Radiograph of the CMC1 joint before (left) and during distraction (right). Published with permission of the original authors and the Journal of Plastic Surgery and Hand Surgery www.tandfonline.com (reference 19)

**Fig. 3 Fig3:**
[figure not shown]
Standard Protocol Items: Recommendations for Interventional Trials (SPIRIT) figure showing the phases of the trial and data collection time points

### Study parameters

#### Primary parameter

The primary parameter is physical function at 1 year measured with the Patient-Reported Outcomes Measurement Information System Physical Function for the Upper Extremity (PROMIS UE) [25]. This is a validated 16-item questionnaire answered on a 5-point Likert scale. The PROMIS UE has *T*-scores with a mean of 50, and higher scores indicate better physical function.

#### Secondary study parameters

Patient characteristics: gender, age at operation, work status, marital status, and level of highest education.Michigan Hand Outcome Questionnaire (MHQ - Dutch Language Version): a validated 57-item questionnaire that gauges hand health status on a scale from 0 to 100 with higher scores indicating better hand health status [26].Patient Health Questionnaire (PHQ-2): 2-item questionnaire with scores from 0 representing ‘lowest level of depression’ to 6 ‘highest level of depression’ [27].Pain Catastrophizing Scale (PCS-4): 4-item questionnaire rated on a 5-point Likert scale with scores ranging from 0 indicating ‘no catastrophic thinking’ to 16 ‘worst possible catastrophic thinking’ [28].Visual analogue scale (VAS) scores for pain, patient satisfaction, thumb stiffness and function: with scores from 0 representing ‘no pain at all’ or ‘fully satisfied’ or ‘no stiffness at all’ or ‘optimal function’ to 100 ‘worst pain possible’ or ‘not at all satisfied’ or ‘worst stiffness possible’ or ‘worst possible function’.Range of motion obtained by an independent certified hand therapist:Thumb opposition by Kapandji scores (range 0–10)Palmar thumb abduction (degrees) by Pollexograph [29]Strength measures* (in kg) obtained by an independent certified hand therapist:Grip strength measured with a Jamar hand dynamometerKey and tip pinch strength measured with baseline pinch gauge**Strength measures are recorded as the average of three attempts*Radiographs will be obtained in three different views (posteroanterior, lateral and Bett’s view). Joint space (in mm) will be scored by an independent blinded radiologist.Adverse events: classified according to the Clavien-Dindo classification of surgical complications ranging from grade I (minor complication) to grade V (death) [30]. Any adverse event that occurs during the distraction period or at follow-up will be administered and classified. For example, pin tract infections that are adequately treated with oral antibiotics will be classified as grade I (minor complication). In the unlikely event that intravenous antibiotics and a hospital admission is needed, this will be rated as a grade II complication.Treatment failure: defined as conversion to an invasive surgical procedure (f.e. trapeziectomy) after distraction therapy due to ongoing symptoms of CMC1 OA.

### Study phases

#### Recruitment and consent

Patients visiting the plastic surgery outpatient clinic of the St. Antonius Hospital in the Netherlands due to symptoms of CMC1 OA will be screened for eligibility. A radiograph is taken at initial visit as standard of care. The hand surgeon will assess eligible patients for enrolment based on the set inclusion and exclusion criteria. Patients who fulfil the inclusion criteria will be invited to participate in the study. Written informed consent will be obtained by the coordinating investigator from all participants.

#### Preoperative measurements

Patients will be asked to complete a series of questionnaires on REDCap, a secured web-application for clinical research, including patient demographics (gender, age, marital status, etc.), physical function, pain scores, and symptoms of depression. All questionnaires are described in detail under ‘study parameters’. Thereafter, patients will visit the hand therapist for strength and range of motion measures of both hands. Next, placement of the distraction device is scheduled and patients will be seen by the anaesthesiologist for screening and approval of the surgical procedure.

#### Postoperative appointments and measurements

The study phases and data collection time points are shown in Fig. 3. The Standard Protocol Items: Recommendations for Interventional Trials (SPIRIT) checklist is provided as Additional file 1. In case of any problems or concerns regarding the distraction device, extra visits will be scheduled if needed.

After placement of the distractor device, a thermoplastic splint is applied and hygiene instructions are given. Patients can go home on the same day of surgery. It is not allowed to drive a car, lift objects or bear weight with the operated hand during the duration of distraction therapy. Three weeks (for group A) or 4 weeks (for group B) after placement of the distractor device, patients are seen at the outpatient clinic. Only VAS pain scores will be collected at this time point and no other questionnaires or measurements are assessed. Any adverse events will be registered if needed.

The distractor device will be removed at the outpatient clinic after 6 weeks for patients in group A and after 8 weeks for patients in group B. After removal, a radiograph is obtained and hand therapy commences according to a standard protocol for rehabilitation after surgical intervention. Patients are informed not to perform heavy weight bearing exercises of the thumb and index finger up to 12 weeks after removal of the distractor device. There is no other relevant concomitant care permitted or prohibited during the trial. A short overview of the exercises and timeline is provided in Additional file 2.

At 3 months, 6 months, and 1 year after placement of the distractor device (regardless of group), patients will be seen for follow-up measures at the outpatient clinic. At these visits, several questionnaires will be completed, radiographs of the thumb will be obtained, and any adverse events that may have occurred will be evaluated and registered. The same measurements are collected at 2 years and 5 years after initial surgery to evaluate the long-term effects of joint distraction. If patients underwent other surgical interventions for ongoing symptoms of CMC1 OA, despite joint distraction of the affected hand, this will be registered as treatment failure.

Patients will receive an invitation letter for their next follow-up appointment. We will call or mail those who do not follow-up and cannot be reached. Patients are always able to contact the investigator or the St. Antonius Hospital for any reason, question, or problem.

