### Statistical analysis

The following characteristics will be reported in the baseline characteristics table: age, gender, work status, marital status, level of education, PROMIS UE scores, MHQ, PHQ-2, PCS-4, VAS for pain, satisfaction, thumb stiffness, thumb function, range of motion, strength, and joint space width on radiographs. Testing for differences in baseline characteristics among groups will only be done if visual inspection of the results indicates possible significant differences.

The primary outcome will be the difference in PROMIS UE score between the 6-week group (A) and 8-week group (B) at 1 year follow-up. We will report the mean with SD and 95% CI and the mean difference with 95% confidence interval. If the mean difference with 95% CI falls within the predefined non-inferiority margin of 9.0 points of PROMIS UE scores, we will conclude non-inferiority.

Regarding the secondary hypotheses, we will test for superiority between the 6-week and 8-week group.
We will assess any differences in MHQ scores, VAS pain, VAS satisfaction, VAS function, VAS stiffness, range of motion, and strength at 1 year follow-up compared to baseline. We will test for superiority between groups by comparing the mean differences at 1 year.Treatment failure is scored when a patient proceeds with an invasive surgical procedure (f.e. trapeziectomy) after distraction therapy due to ongoing symptoms of CMC1 OA. We will analyse the difference between groups in the proportion of participants who are classed as treatment failure at 1 year.Adverse event rates will be reported and classified according to the Clavien-Dindo classification of surgical complications. We will analyse the difference between groups in the proportion of participants who are classed as adverse event at 1 year.Joint space width at 1 year follow-up is compared to baseline measures in both groups. Mean difference in mm between groups is assessed at 1 year follow-up.

This will be intention-to-treat analyses. In case of non-adherence, to test the robustness of our results, we will also report the results of per-protocol analyses [33].

We will create 2 multivariable linear regression models to assess factors independently associated with PROMIS UE and MHQ scores at 1 year. In these models, we will include all mentioned study parameters (except PROMIS UE and MHQ scores) with *P* < 0.10 in bivariate analysis. *P* values < 0.05 are considered statistically significant.

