We will perform the same statistical tests and analysis as mentioned above at 2 years and 5 years post-distraction to study the long-term results. Incomplete data will be adequately described. We will use multiple imputation for any missing data or means for missing values.

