## Discussion

Joint distraction is a fairly new treatment for patients with CMC1 OA [19]. To our knowledge, to date, 52 patients have been treated with joint distraction. In contrast to other joint distraction treatments, CMC1 distraction is not offered in regular clinical practice yet, only in study context. Distraction therapy can result in less pain and better physical function and can therefore postpone an invasive surgical intervention [12–16, 18]. In a previous study about CMC1 joint distraction, a surgical intervention was postponed for at least 2 years in most (19 of 20) patients (unpublished data).

This trial will test if we can decrease the current distraction duration from 8 to 6 weeks and still achieve sufficient clinical benefits for patients. For knee distraction, a decreased treatment duration of 6 weeks (instead of 8 weeks) resulted in less pin tract infections while good clinical results were still achieved [17, 18]. Therefore, knee distraction is nowadays applied for 6 weeks. It is unknown if 6 weeks of continuous CMC1 joint distraction, compared to 8 weeks, leads to similar results: less adverse events and sufficient clinical benefits (e.g. less pain and better physical function). The outcomes of this study will give a more decisive answer to this question. If safe, the duration of basal thumb joint distraction can be reduced to 6 weeks, reducing patient burden.

This study will also enable to assess the short- and long-term effects of joint distraction in 68 patients. We expect that joint distraction will lead to less pain and better physical function in patients on average, regardless of group. Because this is a relatively new treatment, this trial will provide greater knowledge of potential adverse events. This knowledge allows for more informed decision making for patients considering CMC1 distraction treatment and will help to better define the place of joint distraction in treatment of CMC1 OA.

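### The 2- and 5-year scores are presented as effects of joint distraction, but nothing separates scores measured after conversion to trapeziectomy or other surgery

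*Protocol article*

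**What the plan says.** - **Purpose.** Study objectives introduces the later time points with "To study the long-term effects of joint distraction in the treatment of CMC1 OA" and has all hypotheses tested again at 2 and 5 years. Postoperative appointments and measurements says "The same measurements are collected at 2 years and 5 years after initial surgery to evaluate the long-term effects of joint distraction". The Discussion adds "This study will also enable to assess the short- and long-term effects of joint distraction in 68 patients", and 68 is the full planned enrolment.
- **Analysis.** Statistical analysis sets intention-to-treat, adds per-protocol results where there is non-adherence, and then says "We will perform the same statistical tests and analysis as mentioned above at 2 years and 5 years post-distraction to study the long-term results".
- **Conversion.** Secondary study parameters has treatment failure "defined as conversion to an invasive surgical procedure (f.e. trapeziectomy) after distraction therapy due to ongoing symptoms of CMC1 OA". At follow-up visits, when a patient has had other surgery for ongoing symptoms, "this will be registered as treatment failure". Its only stated analysis is as a proportion: "We will analyse the difference between groups in the proportion of participants who are classed as treatment failure at 1 year".

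The article gives no rule for PROMIS UE, MHQ, VAS, strength or range-of-motion values measured after conversion.

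**The concern.** The Background says that distraction is meant to postpone or prevent invasive surgery, and every patient enters with an established indication for such surgery. Conversion is therefore the foreseeable route for a failed distraction, and it is itself an active treatment of the same symptoms. A 5-year pain or function score taken after a trapeziectomy largely reflects that operation. Where the operation works, failures of distraction raise the mean reported under distraction's name. Range of motion can move the other way: the Background notes that "Arthrodesis of the CMC1 joint reduces range of motion".

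Two readings are at stake. One is descriptive: how patients do in the long term on distraction, in each arm and overall. The other is comparative: the non-inferiority question is asked again at 2 and 5 years. If 6 weeks were less durable and led to more conversions, successful later surgery would pull that arm's mean back up and make non-inferiority easier to conclude.

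**Working it through.** **1. Do converted thumbs enter the score means?** No single sentence says so; it follows from four statements together. The analysis is intention-to-treat, the same tests are repeated at 2 and 5 years, the long-term effects are to be assessed in all 68 patients, and conversion is only recorded and counted. The per-protocol run does not separate these scores: a patient who completes 6 or 8 weeks and is operated on later has adhered.

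**2. The plan's own figure.** With margin 9.0, SD 11, true difference 0, one-sided 2.5% and 90% power, n per arm = 2 × 11² × (1.960 + 1.282)² / 9.0² = 31.4, so 32. The total is 64, and 64 / 0.95 = 67.4, so 68. This matches the protocol and is not in dispute; it gives the scale for what follows.

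**3. Inputs on conversion (Background).**
- CMC1, 2 years: 1 of 20 converted, 5% (exact 95% CI 0.1% to 24.9%).
- CMC1, 5 years: 0 of the first 5 (exact one-sided 97.5% upper limit 52%).
- Other-joint distraction: 8/17 joints surviving at 9 years. That sentence does not name the joint; the surrounding text concerns ankle and knee.

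The documents give no figure for the score gain after conversion. I assume 9.0 points, the protocol's MCID, and show a range below.

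**4. Shift in the overall mean** = proportion converted × gain, relative to the score without the later surgery. Under a constant hazard h, the proportion by time t is 1 − exp(−h·t).
- CMC1: h = −ln(0.95)/2 = 0.0256 per year.
- Other joint: h = −ln(8/17)/9 = 0.0838 per year.

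| Source of hazard | Time | Converted | Of 68 | Shift at 9.0 points |
|---|---|---|---|---|
| CMC1, 1 of 20 | 2 y | 5.0% | 3.4 | 0.45 |
| CMC1, 1 of 20 | 5 y | 12.0% | 8.2 | 1.08 |
| Other joint, 8/17 | 2 y | 15.4% | 10.5 | 1.39 |
| Other joint, 8/17 | 5 y | 34.2% | 23.3 | 3.08 |

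For assumed gains of 4.5 to 18 points, the shift is 0.2 to 0.9 at 5% converted, and 1.1 to 4.5 at 24.9% (the upper limit for 1 of 20).

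**5. Does 0 of 5 at 5 years settle it?** No. The chance of seeing it is exp(−0.0256 × 25) = 0.53 under the CMC1 hazard and exp(−0.0838 × 25) = 0.12 under the other-joint hazard. It leans towards the lower figure but excludes neither.

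**6. Between arms.** Shift in the difference = (conversion in 6-week arm − conversion in 8-week arm) × gain. With equal conversion and equal gain it is zero. For an illustrative 20% versus 5%, it is 0.15 × 9.0 = 1.35 points towards the 6-week arm (0.7 to 2.7 for gains of 4.5 to 18), against a margin of 9.0. If the 8-week arm converted more, the sign would reverse.

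**The case against.** **The article is silent rather than wrong, and handling of scores after conversion may sit in the full protocol or analysis plan.** This stands in part. A reader might infer that the protocol expressly keeps converted thumbs in every score analysis; it does not say so, and a supplementary analysis may exist elsewhere. What does not depend on an unseen document is that the stated purpose (effects of distraction) and the stated analysis (intention-to-treat, repeated unchanged) do not match.

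**Failures are reported in their own right.** True. Conversion is defined, compared between arms and repeated at the later times, so a reading that failures are hidden is not supported. A separate proportion still does not change what the means contain.

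**Intention-to-treat is legitimate here.** This stands in full. Randomisation is to 6 or 8 weeks, and the comparison of those strategies, later surgery included, is valid. It would be wrong to read this point as saying that the long-term comparison is biased for that question. It is also true that no arm goes without distraction, so no handling of conversion makes a within-arm mean a causal effect of distraction, and the Discussion accepts that comparative studies are still needed.

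**The magnitude is assumed.** This stands. The 9.0-point gain has no source in the documents, and the Background mentions persisting symptoms after trapeziectomy, so the gain may be smaller. A shift of about 3 points might be taken as the expected size, but it needs a figure from another joint. The data on this joint point lower, although they are few.

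**Conclusion.** The point holds in a limited form. Followed as written, the plan puts scores measured after later surgery into 2- and 5-year means that are described as long-term effects of distraction, and no stated analysis separates them. Those means are sound as results of a strategy that includes later surgery; they are not results of distraction alone.

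The size is unknown. With the CMC1 figure of 1 of 20, a constant hazard and an assumed 9.0-point gain, the overall PROMIS UE mean is about 0.5 points higher at 2 years and about 1.1 at 5 years, which is small against an SD of 11. About 3 points at 5 years requires the other-joint survival figure to apply. The between-arm effect is zero unless conversion or the gain differs by arm; if the 6-week arm converts more and later surgery succeeds, the shift favours non-inferiority. A reader might conclude that the long-term data can say nothing about lasting benefit. That goes too far: with the conversion proportion beside them and an analysis that counts conversion as failure, they can.

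**What to change.** 1. Keep the intention-to-treat results at 2 and 5 years, and label them as the effect of the 6- or 8-week strategy including any later surgery.
2. Pre-specify, at both times, per arm and between arms, a supplementary analysis that counts conversion as failure. One option is a composite: success means no further surgery on the treated joint and PROMIS UE improved from baseline by at least the protocol's 9.0-point MCID. The other is a rank analysis with converted patients ranked worst, which avoids dichotomising. Fix the choice before conversion counts by arm are known.
3. Do not simply drop converted patients, since that leaves mainly the successes. Do not carry forward the last value before conversion either. After 1 year the scheduled visits are only at 2 and 5 years, so that value may predate the deterioration that led to surgery and could itself flatter distraction.

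Cost: analysis and wording only, as all the data are already planned. The composite is less precise. With 32 evaluable per arm, the 95% half-width for a mean difference is 1.96 × 11 × √(2/32) = 5.4 points. For a difference in success proportions it is at most about 1.96 × √(2 × 0.25/32) = 0.245, or 25 percentage points (worst case, 50% success in each arm), and wider with more loss by 5 years. The long-term figure may also look less favourable.
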